### Concealment mechanism {16b}

Randomization will be performed by a person who will not be engaged in the study and will be blinded to the identity of the participants.

### Implementation {16c}

There will be four arms. The abovementioned interventions will be implemented among the three intervention groups. The control group will only receive usual care.

## Assignment of interventions: blinding

This is not applicable. It is not possible to mask this study because of its nature. To avoid bias in the outcome assessment, research assistants concerned with data collection and/or preparation will be blinded to the allocation of the participants.

### Who will be blinded {17a}

As the RCT is an educational intervention study, blinding of participants and researchers is not possible. To minimize selection bias, we will use randomization.

### Procedure for unblinding if needed {17b}

This is not applicable.

## Data collection and management

### Plans for assessment and collection of outcomes {18a}

The primary outcome of the intervention (mode of delivery) will be measured using a checklist after the childbirth.

The secondary outcomes will be measured by a questionnaire 1 month after the interventions.

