**Methods:**

A four-armed, parallel-design randomized controlled trial will be conducted on pregnant women. One hundred and twenty women will be randomly assigned to four groups including three intervention groups and one control group. The intervention groups included the following: (1) motivational interviewing; (2) face-to-face information, motivation, and behavioral skills model; and (3) information, motivation, and behavioral skills model provided using a mobile application. The inclusion criteria include being literate, being in gestational age from 24 to 32 weeks, being able to speak Persian, having no complications in the current pregnancy, having no indications for Cesarean section, and having enough time to participate in the intervention. The primary outcome of the study is the mode of delivery. The secondary outcomes are women’s intention to undergo Cesarean section and women’s self-efficacy.

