### Eligibility criteria {10}

#### Inclusion criteria

The criteria for entering women are being literate, being in gestational age 24 to 32 weeks, being able to speak Persian, having no complications in the current pregnancy, having no indications for CS, and having enough time to participate in the interventions.

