### Intervention description {11a}

The content of interventions will be designed based on a qualitative evidence synthesis and a quantitative systematic review and meta-analysis in Iran [55]. Also, we will design the interventions tailored to the participants’ needs. The interventions are expected to take around 2 months to be completed, and women will be followed up until their delivery time.Motivational interviewing (MI)In this intervention group, pregnant women will be trained face-to-face based on the MI. During three 45–60-min sessions, MI techniques will be provided to the participants. MI is a directive, client-centered counseling style for eliciting behavior change by helping clients to explore and resolve ambivalence. It is most centrally defined not by technique but by its spirit as a facilitative style for interpersonal relationships. MI is a relatively simple, transparent, and supportive talk therapy based on the principles of cognitive-behavior therapy. In this group, we will help women to explore and resolve ambivalence about the mode of delivery and build their intrinsic motivation.We will not force women to choose a specific mode of delivery. We will ask open-ended questions (for example, “Tell me what you think about CS?” or “What do encourage you to choose this type of delivery (CS or NVD)?”). Open-ended questions can help us to understand how they are thinking about the mode of delivery. Affirming is one of the fundamental MI skills. We will use it to support engagement, encourage the women to further explore change processes, and build confidence. We will find an opinion the client is making or a strength she will notice and reflect it to her (for example, “So how did you manage to control your fear after attending our training sessions?”). We will use reflective listening as a simple method to reduce resistance in MI. The last step of this technique is to summarize what the pregnant women have said.Information, motivation, and behavioral skills model through a face-to-face approach (IMB)During three 45–60-min sessions, the model’s strategies will be provided to the participants. Participants will receive information and behavioral skills related to the choice of mode of delivery as well as internal and external motivational factors related to the choice of delivery. The strategy includes the following: (1) *Information*—the intervention will begin with information on the prevalence of CS and CS-related complications in women, and outcome of unnecessary CS; (2) *Motivation*—the interventionist will perform this technique to motivate pregnant women, providing personal feedback, asking open-ended questions, affirming desirable behavior, reflective listening, working at the women’s pace, and negotiating goals that will be realistic and attainable; and (3) *Behavioral skills*—women will be given behavioral skills training on how to control the obstacle of NVD. To build skills for choosing the mode of delivery, training will be given on how to reduce these barriers.Information, motivation, and behavioral skills model through mobile app (IMB-App)The mobile application (M-health) has been designed based on the IMB model. The software will be installed on mobile phones of participants in the group, and its operation will be taught individually. Women will work with the application in the presence of the research team, and any existing problems will be resolved. The strategies foreseen for adherence improvement include reminders set at defined intervals in the form of pop-up messages. To monitor adherence, the data collected on the server will be used. In addition to the application, a server will be designed in which the users’ activities will be collected. Items such as the duration of application usage and the sections used by the user (in addition to registering their time and duration) will be registered. Every time the user’s mobile is connected to the Internet, the data will be uploaded and saved on to the server. These data can be used as a proxy of adherence to the intervention.

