
*Control group*: without any intervention

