### Criteria for discontinuing or modifying allocated interventions {11b}

The intervention will be discontinued based on the participant’s request, or if a woman undergoes birth.

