#### Questionnaire

The questionnaire contains the women’s demographic and obstetrics history information, self-efficacy [56] in CS, and intention [57]. Demographic and obstetrics history items include age, income, educational level (pregnant women and their spouses), employment status (pregnant women and their spouses), number of births, number of pregnancies, current gestational age, number of live children, history of infertility, history of illness, date of birth, and participating in birth classes.

The questionnaire also consists of 17 items about self-efficacy and one item about intention of the women. To measure women’s self-efficacy, we used the Iranian version of the Childbirth Self-Efficacy Inventory (CBSEI) [56]. The instrument was originally developed by Lowe to measure maternal confidence in coping abilities during labor [58]. Khorsandi et al. examined the psychometric properties of the Iranian version and reported that this version was acceptable, reliable, and valid to measure women’s self-efficacy. Items were Likert-type questions, ranging from 1 to 10. Intention was measured using a single item questionnaire [57]. Several studies have found that single item questionnaires would be sufficient to measure some constructs [59].

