### Plans to promote participant retention and complete follow-up {18b}

We will follow the participants until the time of delivery. The pregnant women will be participated in this study after ensuring that they have met the study criteria. They will complete informed consent forms. In the first visit, the baseline measurement will be completed by the researcher. During the second visit, the application will be installed on cell phones of the IMB-App group and its operation will be taught to them.

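### The secondary-outcome questionnaire falls at about 37–45 weeks of gestation, after birth for a large share of women, and has no defined date in the control arm

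*Protocol article*

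**What the plan says.** Four statements in the Protocol article fix the timing.

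- Entry (Inclusion criteria): "being in gestational age 24 to 32 weeks".
- Length of the course (Intervention description {11a}): "The interventions are expected to take around 2 months to be completed".
- Assessment (Plans for assessment and collection of outcomes {18a}): "The secondary outcomes will be measured by a questionnaire 1 month after the interventions".
- End of follow-up (Plans to promote participant retention {18b}): "We will follow the participants until the time of delivery".

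The abstract names what is measured: "The secondary outcomes are women’s intention to undergo Cesarean section and women’s self-efficacy". The self-efficacy inventory was developed to "measure maternal confidence in coping abilities during labor" (Questionnaire). Data management {19} says that follow-up uses the same questionnaires as baseline. The control group is described as "without any intervention", and Outcomes {12} compares intervention and control groups before and after the interventions.

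The article gives no gestational age for the questionnaire, no rule to bring it forward if birth is near, and no rule for women who deliver first.

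**The concern.** Both secondary outcomes presuppose a birth still to come. A woman who has delivered no longer has an intention about mode of delivery, and her confidence in coping with labor is now a judgement on a labor, or an operation, that has taken place. If the schedule puts the questionnaire after birth, her outcome is either missing or a different quantity under the same name. No analysis can recover an intention that was never recorded before delivery.

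With 30 women per arm there is little to spare. The control arm adds a second problem: a date defined by the end of the interventions does not exist for women who receive none, so the comparison with control has no common time point.

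**Working it through.** **Inputs from the article.** Entry week E from 24 to 32; course of two months; lag of one month; 30 women per arm.

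**Assumptions, because the article gives no figure.** Length of a month m: 4 weeks, or 365.25/84 = 4.348 weeks. Week of birth b: 38 to 40, with 41 as a further check (women with preterm labor are excluded, so analysed births are taken as term). Entry: uniform over 24–32 weeks, then skewed early or late.

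**Step 1: when the questionnaire falls due.** Q = E + 3m.

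- Calendar months: 24 + 13.04 = 37.0 weeks to 32 + 13.04 = 45.0 weeks.
- Four-week months: 24 + 12 = 36 weeks to 32 + 12 = 44 weeks.

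**Step 2: share due after birth, uniform entry.** The latest entry that still allows an answer before birth is b − 3m, so the share is (32 − (b − 3m))/8.

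| Birth week | Calendar months | Four-week months |
|---|---|---|
| 38 | (32 − 24.96)/8 = 88% | (32 − 26)/8 = 75% |
| 39 | (32 − 25.96)/8 = 76% | (32 − 27)/8 = 63% |
| 40 | (32 − 26.96)/8 = 63% | (32 − 28)/8 = 50% |
| 41 | (32 − 27.96)/8 = 51% | (32 − 29)/8 = 38% |

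For birth at 39 weeks, only women who entered by about week 26 (calendar) or 27 (four-week) could answer in time.

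**Step 3: other entry patterns.** Birth week was simulated as normal with mean 38.5 to 40 and SD 1.0 to 1.2, truncated below at 37 weeks. Entry was uniform, or triangular with its peak at 24 or at 32 weeks.

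| Entry | Calendar months | Four-week months |
|---|---|---|
| Uniform | 63–80% | 50–67% |
| Skewed early | 42–65% | 27–46% |
| Skewed late | 84–95% | 73–88% |

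**Step 4: what is left per arm.** A share of 50–88% after birth leaves 30 × 0.50 = 15 down to 30 × 0.12 = 3.6 women with an answer before birth. At 27–65% the figures are 30 × 0.73 = 21.9 down to 30 × 0.35 = 10.5.

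**Step 5: does dropping the lag suffice?** At the end of the course the share already past birth is (32 − (b − 2m))/8. For birth at 38, 39 and 40 weeks this is 34%, 21% and 9% with calendar months, and 25%, 13% and 0% with four-week months. The loss shrinks a good deal but does not vanish, so the entry window and course length have to be looked at too.

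**The case against.** **The course may be shorter than two months.** The figure is an expectation, the face-to-face arms have three sessions of 45–60 minutes, and the Discussion calls the intervention brief. A four-week course would put the questionnaire at about 32 to 40 weeks. That would remove most of the problem, but the article states two months and no session spacing that would support a shorter reading.

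**That most women would be due after birth is not established.** A reader might infer it from the 37–45 week window. It also needs the week of birth and the spread of entry, which the article does not give. With early entry, or with four-week months and birth at 41 weeks, the share falls below half. This part of the objection stands; a large share is supported, a majority only under stated assumptions.

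**Loss related to the choice of Cesarean section is not documented.** A reader might infer that women with a scheduled operation deliver first and so drop out of the questionnaire selectively. Nothing in the article gives the timing of births by mode, so the direction of any bias is not claimed here.

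**Two further readings go too far.** Criteria for discontinuing {11b} ends the intervention on request "or if a woman undergoes birth"; that is a stopping rule and contradicts nothing, though it does not reschedule the questionnaire either. Nor does the article show that the three active arms would be assessed at different gestational ages, since one expected duration covers them all. Only the control date is undefined.

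**An article condenses.** A full protocol could hold a control-arm date. It would not remove the conflict among the entry window, duration and lag printed here.

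**Conclusion.** The timing is wrong as written. The 37–45 week window (36–44 with four-week months) follows from the article's own figures, and for women entering late in the window it lies beyond any birth week considered. The share affected rests on assumptions: about 50–88% with uniform entry and birth at 38 to 40 weeks, about 27–65% with entry skewed early. Even the low end is too large for two outcomes that lose their meaning at delivery, and a questionnaire weeks after birth does not fit follow-up that stops at delivery. The rule also leaves the control arm without a date. The damage is confined to the secondary outcomes; mode of delivery is recorded after childbirth in every arm and is untouched.

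**What to change.** 1. Drop the one-month lag. Set the questionnaire on one clock common to all four arms: for example a fixed interval from randomisation that matches the end of the course, or a fixed late-pregnancy prenatal visit if that comes first. Every woman, including controls, then has a date.
2. Reconcile the Inclusion criteria, Intervention description {11a}, assessment plan {18a} and follow-up statement {18b}, so that entry window, course length and assessment date are compatible and the questionnaire precedes birth for nearly all women. Which of them gives way is for the trial team to decide.
3. Record the assessment date relative to the date of birth, also for women already enrolled. Report by arm how many were not assessed before delivery, and do not treat answers given after birth as intention. Setting those answers aside selects on an event after randomisation, so this step shows the loss but does not cure it; the timing change has to do that.

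**Cost.** An amendment to the assessment schedule, with no extra visit if it is tied to usual prenatal care. The lag after the last session becomes shorter, and some late entrants would be assessed at or before the end of the course. As an illustration, a visit at 35–36 weeks precedes the end of an 8.7-week course for anyone entering after 26.3–27.3 weeks, which under uniform entry is (32 − 27.3)/8 = 59% to (32 − 26.3)/8 = 71% of women. An early visit alone is therefore no complete remedy, and the entry window may have to narrow.

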#### Questionnaire

The questionnaire contains the women’s demographic and obstetrics history information, self-efficacy [56] in CS, and intention [57]. Demographic and obstetrics history items include age, income, educational level (pregnant women and their spouses), employment status (pregnant women and their spouses), number of births, number of pregnancies, current gestational age, number of live children, history of infertility, history of illness, date of birth, and participating in birth classes.

The questionnaire also consists of 17 items about self-efficacy and one item about intention of the women. To measure women’s self-efficacy, we used the Iranian version of the Childbirth Self-Efficacy Inventory (CBSEI) [56]. The instrument was originally developed by Lowe to measure maternal confidence in coping abilities during labor [58]. Khorsandi et al. examined the psychometric properties of the Iranian version and reported that this version was acceptable, reliable, and valid to measure women’s self-efficacy. Items were Likert-type questions, ranging from 1 to 10. Intention was measured using a single item questionnaire [57]. Several studies have found that single item questionnaires would be sufficient to measure some constructs [59].

### Plans to promote participant retention and complete follow-up {18b}

We will follow the participants until the time of delivery. The pregnant women will be participated in this study after ensuring that they have met the study criteria. They will complete informed consent forms. In the first visit, the baseline measurement will be completed by the researcher. During the second visit, the application will be installed on cell phones of the IMB-App group and its operation will be taught to them.

### Data management {19}

To ensure that the data is correctly entered, a double entry of data will be performed by two different individuals. Pregnant women who refer to the hospital will be registered, by chronological order of selection, and they will be allocated randomly in each group. All data obtained from women will be entered to SPSS software. A code will be defined to identify missing data. After screening the data and preparing the data for statistical analysis, first using descriptive statistics such as frequency tables, means and standard deviation, and bar chart and histogram, the distribution of variables will be checked. The obtained data will be kept strictly confidential and will be stored with secured and restricted access; also, the signed consent will be kept locked. Follow-up data are received using the same questionnaires as used at baseline.

### Confidentiality {27}

Only researchers will have access to the personal data in the trial. These data will not be published, and they will be discarded after the publication of results.

### Plans for collection, laboratory evaluation, and storage of biological specimens for genetic or molecular analysis in this trial/future use {33}

This is not applicable. Researchers confirm that there are no laboratory and storage of biological specimens for genetic or molecular analysis in this study.

## Statistical methods

### Statistical methods for primary and secondary outcomes {20a}

Data will be analyzed using descriptive statistics (mean, frequency, and standard deviation); inferential statistics including independent *t* test, paired *t* test, chi-squared, and one-way ANOVA tests; and logistic regression modeling to examine the factors affecting the women’s choice on the mode of delivery to examine the simultaneous effect of variables on the chances of choosing CS. The significance level of the tests will be considered as less than 0.05.

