### Outcomes {12}

Determining and comparing the effects of MI, IMB, and IMB-App on mode of delivery in the target and control groups before and after the interventions.Determining and comparing the effects of MI, IMB, and IMB-App on the intention of performing CS in women in the target and control groups before and after the interventions.Determining and comparing the effect of MI, IMB, and IMB-App on women’s self-efficacy in target and control groups before and after the interventions.

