## Assignment of interventions: allocation

### Sequence generation {16a}

The participants will be randomly assigned to four groups after the initial assessment and upon completing the baseline data form. We will recruit the participants based on the registration order of women with the clinic, and no other factor will contribute to participants’ order on the list. Each participant on the list will be assigned a consecutive research identification number according to the order by which they will be registered with the clinic. The first participant on the list will be randomly assigned to the MI intervention group, and the next two participants will be assigned to the IMB and IMB-App interventions, respectively. The fourth participant will be assigned to the control group.

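### The listed tests include no baseline-adjusted between-arm analysis for self-efficacy and intention, although both are measured before allocation

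*Protocol article*

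**What the plan says.** All references are to the protocol article.

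- **Baseline.** Under participant retention {18b}: "In the first visit, the baseline measurement will be completed by the researcher". Sequence generation {16a} puts this before allocation: women are "randomly assigned to four groups after the initial assessment and upon completing the baseline data form". Data management {19} adds: "Follow-up data are received using the same questionnaires as used at baseline".
- **Follow-up.** Under assessment of outcomes {18a}: "The secondary outcomes will be measured by a questionnaire 1 month after the interventions". This is a single follow-up measurement.
- **Aim.** Outcomes {12} sets out to compare the interventions on intention and on women's "self-efficacy in target and control groups before and after the interventions".
- **Analysis.** Statistical methods {20a} names "inferential statistics including independent *t* test, paired *t* test, chi-squared, and one-way ANOVA tests" at the 0.05 level. The only multivariable model is a logistic regression, and it concerns mode of delivery.

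Section {20a} does not say which test serves which outcome or time point.

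**The concern.** Self-efficacy and intention are the only outcomes measured twice, so the paired t test must be meant for their before-to-after change. Taken arm by arm, that test has no control group. Scores may move in all arms as birth approaches or on retesting, and a paired test in an active arm cannot separate such drift from an effect. Section {20a} lists it beside the between-arm tests, at the same 0.05 level and without a descriptive label, which invites its use as evidence of effect.

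The between-arm tests that are listed, independent t and one-way ANOVA, contain no term for baseline. With 30 women per arm precision is scarce, and a covariate that is collected before allocation and is probably prognostic would go unused.

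**Working it through.** **Inputs from the protocol.** 30 women in each of 4 arms and 80% power (Sample size {14}); significance level 0.05 (Statistical methods {20a}), taken as two-sided; baseline before allocation and one follow-up.

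**Assumptions, because the protocol gives no values.** Correlation r between baseline and follow-up score, 0.3 to 0.7; drift common to all four arms, 0 to 0.5 SD in the table and up to 0.8 SD at r = 0.5.

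**The plan's own figure.** The stated size cannot be reproduced, because the minimum difference has no value, SD or outcome attached. Solving backwards for two arms on a continuous score:

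detectable difference = (1.96 + 0.84) × √(2/30) = 0.72 SD.

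**Step 1: precision.** Relative to follow-up scores alone, the variance of the arm difference is multiplied by 1 − r² for ANCOVA and by 2(1 − r) for change scores. The detectable difference is 0.72 times the square root of that factor (normal approximation).

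| r | ANCOVA factor | Change-score factor | Follow-up only | Change score | ANCOVA |
|---|---|---|---|---|---|
| 0.3 | 0.91 | 1.40 | 0.72 SD | 0.86 SD | 0.69 SD |
| 0.5 | 0.75 | 1.00 | 0.72 SD | 0.72 SD | 0.63 SD |
| 0.7 | 0.51 | 0.60 | 0.72 SD | 0.56 SD | 0.52 SD |

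At a true difference of 0.5 SD, power is 49% with follow-up scores alone. With change scores it is 37%, 49% and 71% at the three correlations, and with ANCOVA 53%, 61% and 77%. In sample-size terms, ANCOVA on 30 per arm is worth 30/0.91 = 33, 30/0.75 = 40 or 30/0.51 = 59 per arm analysed on follow-up alone.

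**Step 2: paired tests read as effects.** Suppose no arm differs from another and all drift equally. Let q be the probability that one arm's paired test is not significant. The probability that at least one of three active arms is significant while control is not is

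q × (1 − q³) = q − q⁴.

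- No drift: q = 0.95, so 0.95 × (1 − 0.857) = 0.135.
- Drift 0.3 SD, r = 0.5: the change has SD √(2 × 0.5) = 1, so the noncentrality is 0.3 × √30 = 1.64. The paired test is significant with probability 0.355, q = 0.645, and q − q⁴ = 0.472.
- Maximum over all drifts: 1 − 4q³ = 0 gives q = 0.63 and 0.63 × 0.75 = 0.47. The second case is therefore essentially the worst case.

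Simulation with 20,000 replicates gives, in per cent of trials:

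| r | drift 0 | 0.2 SD | 0.3 SD | 0.4 SD | 0.5 SD |
|---|---|---|---|---|---|
| 0.3 | 13.5 | 32.4 | 44.8 | 46.3 | 36.5 |
| 0.5 | 13.4 | 37.7 | 47.4 | 39.6 | 24.1 |
| 0.7 | 13.6 | 44.5 | 41.6 | 21.5 | 7.3 |

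With larger drift the control arm becomes significant too and the pattern fades: at r = 0.5 it is about 1% at 0.8 SD.

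**The case against.** The strongest reply is that section {20a} gives an open list and ties no test to an outcome. It includes between-arm tests, and ANOVA could be run on change scores, which do use baseline. With random allocation, an unadjusted comparison of follow-up scores is unbiased. The mapping of tests to outcomes may sit in an analysis plan that is not shown.

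Much of this stands. The loss is one of efficiency, small at r = 0.3, and it touches secondary outcomes only. But the protocol names its tests, so this is a comment on stated methods. Change scores do not remove the loss either, since ANCOVA is more precise at each correlation shown.

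Three stronger readings are tempting, and the document does not support them.

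- A reader might infer that effects will be claimed wherever an active arm has a significant paired test and control does not. The protocol proposes no such rule, and the figures in step 2 apply only if the listed between-arm tests are disregarded.
- A reader might infer that the logistic regression, intended "to examine the simultaneous effect of variables on the chances of choosing CS", will take in every background item of the questionnaire and be overfitted. Section {20a} does not say which variables enter. The number of vaginal births is not fixed either: the quoted private-hospital Cesarean rates are general ones, whereas the trial enrols women without an indication and offers 90 of 120 an intervention meant to lower the rate.
- A reader might see an analytic error in the aim to compare effects "on mode of delivery in the target and control groups before and after the interventions". The wording is loose for an event that happens once, but section {18a} fixes it as recorded after childbirth, so no analysis changes.

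**Conclusion.** The point holds as an improvement to the stated analysis of the two secondary outcomes. No listed method adjusts an arm comparison for the baseline score, although that score is available before allocation. At 80% power, ANCOVA would lower the detectable difference from 0.72 SD to between 0.69 and 0.52 SD for correlations of 0.3 to 0.7. The size of the gain rests on a correlation that the protocol does not give.

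The risk from paired tests is conditional. If they are read as evidence of effect, the misleading pattern occurs in 13.5% of null trials without drift, peaks at about 47% with moderate drift, and falls again with large drift. The plan invites that reading but does not commit to it. Nothing here shows bias in the planned between-arm tests or a fault in the analysis of mode of delivery.

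**What to change.** In Statistical methods {20a}, for each secondary outcome:

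- Name as the main analysis a between-arm model of the follow-up score, with arm (three indicators against control) and baseline score as terms. ANCOVA suits self-efficacy. For intention, a single item, use an ordinal or other suitable baseline-adjusted model.
- Report each active-minus-control contrast with its 95% confidence interval (on the scale of the chosen model for intention).
- Keep paired t tests, if wanted, as descriptive summaries of change within arms, and state that they are not evidence of effect.

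The cost is a few lines of wording. The baseline and follow-up questionnaires are already planned, so no visit, item or participant is added.
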